#### Sensitivity analysis

Sensitivity analyses are performed to assess the robustness of the primary analysis using multiple imputations and assumptions regarding the missing data.

### Safety

All the exercise is completed under the supervision of the designated doctor, and the patient’s heart rate is monitored synchronously. When the patient’s heart rate reached 80% of their reserve heart rate, the patient would exercise temporarily, the heart rate monitoring would be maintained, and the patient could continue to participate in the test until the stability. Patients who feel various kinds of discomfort can request a temporary test and receive the timeliest corresponding treatment. In the event of an emergency, including but not limited to chest pain, extreme difficulty breathing, nausea, dizziness, or injuries such as falls during exercise, patients will be asked to discontinue the trial. The experimenter will document the patient’s condition and make a clear determination regarding the trial’s continuation.

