**Methods/design:**

A single-blind and randomized controlled trial is used to conduct this study, while the randomization list will be generated using a computerized random number generator and opaque sealed envelopes with group allocation will be prepared. It will be strictly followed to blind the outcome assessors. and until the experiment’s conclusion, participants won’t know which group they are enrolled in. Patients between the ages of 35 and 80 who have stable diseases and have not regularly practiced Baduanjin exercise in the past will be included. They are divvied up into the following five groups at random: (1) The conventional care group (control group, CG), (2) The traditional Baduanjin exercise group (TG), (3) The modified Baduanjin exercise group (IG), (4) The resistance exercise group (RG) (5) The modified Baduanjin exercise combined with resistance exercise group (IRG). Those CG participants only received the usual treatment, while TC, IG, and RG participants exercised 1 h twice a day for 3 months. MRG participants will have a 3-month intervention with 1 h of Modified Baduanjin Exercise and 1 H of Resistance Training for each day. Every week, all groups underwent will supervis one-day training, with the exception of the control group. The Pulmonary Function Testing (PFT), HRCT, and 6MWT are the main outcome variables. The St. George Respiratory Questionnaire and mMRC are used as secondary outcome measures.

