### Intervention

We will regularly provide verbal and visual instructions to all subjects, standardize the movement, strengthen the concept of movement, and establish requirements for the amount and frequency of movement. We will according to the specific needs of each group of the experiment accordingly the intervention wording, to distribute it to all team members to participate in, and all the subjects will be asked to record the action content, and exercise duration/sports strength/sports venues, as well as their movement during or after personal feelings, etc. The specific exercise movements of the three positions of the new Baduanjin are shown in these figures (Figs. 3, 4 and 5).

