#### Modified baduanjin exercise group

IG participants will continue to receive their existing prescription medication, plus an exercise program for three months. IG’s exercise regimen is set to be once a day and twice a day. A steering committee of hospital specialists facilitates weekly training and education courses. Each session will be 60 min in length. Include (1) 10 min of warm-up exercise; (2) 40-minute sports training of Modified Baduanjin; (3) 10 min of relaxing stretching and cooling exercises. Under the doctor’s verbal and visual supervision, the exercise is conducted safely, and their exercise intensity and heart rate are monitored to prevent accidents and ensure the trial ran smoothly.

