#### Resistance exercise group

In addition to resistance training, participants in the RG will continue to take their prescribed medications for three months. We will report on resistance training involving the trapezius/deltoid/biceps/pectoralis major, rectus femoris, gluteus maximus, quadriceps femoris, gastrocnemius, and soleus in previous studies of COPD patients with improved lung and limb function. The intensity of resistance training will be divided into eight levels, with the resistance increasing as the level increases. Three times per week, RG will exercise for one hour. Specifically include: (1) 10 min of warm-up exercise, (2) can involve the above 10 muscles-based resistance training, lasting 40 min. (3) 10 min of related muscle relaxation. Patient surveillance and patient safety are used in the same way as IG.

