#### Modified baduanjin exercise combined with the resistance exercise group

Participants in the IRG will continue to receive prescription medications in addition to three months of Modified Baduanjin and anti-resistance exercises. The exercise program of IRG is set as Baduanjin for 7 days a week and anti-resistance exercise for 3 days a week, with the corresponding exercise twice a day. In addition, once a week, patients will engage in a prescribed training exercise under the supervision of doctors in order to standardize and supervise their exercise. Each session will last 60 min and include: (1) a 10-minute warm-up starter; (2) a 20-minute Modified Baduanjin exercise, the operation is the same as IG group; (3) rest for 5 min. (4) anti-resistance exercise for 20 min. The operation is the same as the RG group. (5) 5 min of relaxation and cooling exercise.

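### The Safety section says all exercise is doctor-supervised with live heart-rate monitoring, but the schedule supervises it about once a week and relies mainly on home exercise

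*Protocol article*

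**What the plan says.** The Safety section opens with a universal statement: "All the exercise is completed under the supervision of the designated doctor". It adds that heart rate is monitored during exercise, and it sets a limit at 80% of the heart-rate reserve.

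Four other places bear on supervision:

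- **Abstract, Methods/design:** "Every week, all groups underwent will supervis one-day training, with the exception of the control group". The same paragraph gives the exercise frequency: "TC, IG, and RG participants exercised 1 h twice a day for 3 months".
- **Section on Modified Baduanjin combined with resistance exercise:** "once a week, patients will engage in a prescribed training exercise under the supervision of doctors". Baduanjin itself is prescribed on every day of the week.
- **Adherence to interventions:** compliance in the exercise groups counts attendance at supervised hospital sessions and completion of daily logs as two separate things. Staff telephone participants at least weekly.
- **Discussion, limitations:** home exercise has priority, compliance may not be well assured, and staff keep in touch by video and telephone.

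The Intervention section fits exercise outside the hospital: "all the subjects will be asked to record the action content, and exercise duration/sports strength/sports venues".

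The section on the Modified Baduanjin group also mentions a doctor's "verbal and visual supervision, the exercise is conducted safely, and their exercise intensity and heart rate are monitored". The traditional Baduanjin and resistance sections adopt the same surveillance.

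**The concern.** The article claims a safeguard that its own schedule does not provide. These are patients whom the Background describes as avoiding exertional dyspnoea. A reader of the Safety section would take every session to be attended by a doctor with live heart-rate monitoring, and would read later safety results in that light. In most sessions nobody may be present to see the threshold crossed.

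The threshold rule has its own fault. At 80% of heart-rate reserve the sentence says the patient goes on exercising for a while. It has no word for stopping or pausing, although the rest of it (monitoring kept up, continuation tied to stability) makes sense only if a pause is meant. This is the only numeric heart-rate limit in the article, and no version of it is addressed to someone exercising at home.

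**Working it through.** The Safety section gives no figure to reproduce. The check is how much of the weekly exercise one supervised session or day can cover.

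**Inputs**

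- Supervision: one day a week for the exercise groups (abstract); once a week for the combined group (its own section).
- Resistance group: "Three times per week, RG will exercise for one hour" in its Methods section, but twice a day in the abstract.
- Modified Baduanjin group: "exercise regimen is set to be once a day and twice a day", so 7 or 14 sessions a week. The traditional Baduanjin section is ambiguous in the same way. The abstract says twice a day.

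**Assumptions:** supervision is weekly; daily means 7 days a week; the abstract's TC is the traditional Baduanjin group (TG elsewhere).

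**Formula:** unsupervised share = (S − V) / S, where S is sessions a week and V is supervised sessions a week.

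| Group | S | V | Unsupervised share |
|---|---|---|---|
| Resistance, Methods frequency | 3 | 1 | 2/3 = 66.7% |
| Modified or traditional Baduanjin, once a day | 7 | 1 | 6/7 = 85.7% |
| Modified or traditional Baduanjin, twice a day, one session supervised | 14 | 1 | 13/14 = 92.9% |
| Modified or traditional Baduanjin, twice a day, both sessions of the supervised day | 14 | 2 | 12/14 = 85.7% |

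At the abstract's frequency the resistance group would also have 14 sessions a week, giving the same 85.7% to 92.9%.

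No share is given for the combined group. Its section has Baduanjin on 7 days, resistance on 3 days, a twice-daily instruction, and one 60-minute session that contains both, so a weekly session count cannot be fixed. Supervision once a week against exercise every day is still not supervision of all exercise.

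On every frequency the article gives, weekly supervision leaves most sessions unsupervised. These are shares of sessions. They do not estimate missed adverse events.

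**The case against.** The strongest counter-case is that the documents already show the intended scope. In the two Baduanjin sections, the sentence before the session description is about weekly courses led by hospital specialists. The session described, and the supervision and heart-rate monitoring that follow, are therefore most naturally those of the weekly course. The Safety section also uses on-site language. On this view one sentence lacks a qualifier, the limitations paragraph openly discloses the home setting, and the heart-rate wording is a translation slip. A similar slip occurs in the next sentence, where patients with discomfort may ask for a temporary test.

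Most of this stands, and it is why the point is minor. It does not remove the contradiction, because the Safety sentence covers all exercise. Nor does the article's general licence to omit detail apply, since this is a positive statement that its own text contradicts. The remote contact in the Discussion has a weekly frequency and mentions no heart-rate monitoring.

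A reader might infer more than the documents support:

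- **Every session is supervised.** Taking the session description to mean each exercise session would make the unsupervised share 0% in the modified Baduanjin, traditional Baduanjin and resistance groups. The weekly-course context, the abstract and the home priority all speak against it.
- **Adverse events are ascertained differently in the control arm.** The control group has no supervised day. However, the twice-monthly classes with sign-in are for all arms, the weekly calls include the control group, and the article lists no safety outcome for comparison between arms. A bias claim would be speculation.
- **Home participants have no cover.** Logs, weekly calls and the promise of treatment for adverse events give partial cover.

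**Conclusion.** The contradiction holds, and its severity is minor. The universal supervision and monitoring statement cannot stand beside weekly supervision and priority to home exercise. With weekly supervision, about 67% of resistance-group sessions at 3 a week and 86% to 93% of modified and traditional Baduanjin sessions at 7 to 14 a week are unsupervised. The spread reflects the article's own conflicting frequencies, which are a separate matter. That one day a week is not all exercise does not depend on which frequency is right.

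Neither the supervision nor the 80% limit is shown to reach home sessions. The limit's wording is defective, but its intent is clear enough that it adds little weight. Outcomes, sample size, randomisation and efficacy analysis are unaffected.

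**What to change.** 1. In the Safety section, restrict the statement on doctor supervision and simultaneous heart-rate monitoring to the weekly supervised sessions.
2. Have the responsible clinicians reword the threshold rule: exercise is paused at 80% of heart-rate reserve and resumes only once heart rate is stable.
3. Give participants a matching pause-and-report instruction for home sessions, and follow it up in the weekly calls already planned under Adherence to interventions.
4. The Trial status section says recruitment was complete at submission, and the intervention lasts three months, so items 2 and 3 help only those still exercising. Where follow-up has ended, report which sessions were supervised, and do not describe the safety results as coming from fully supervised exercise.

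The cost is a few sentences in one section, a short home instruction, and a follow-up question in calls already being made.

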#### Control group

Members of the CG will continue to receive their regular care or medication without intervention for exercise.

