### Criteria for discontinuing or modifying allocated interventions

We will seek consent from participants and conduct the trial after signing the informed consent form, and the individual wishes of the participants will be considered. If the participants do not consent and refuse to participate in the experiment, we will respect their views, postpone or alter the intervention, and report the exact reasons. The trial will be stopped if a participant is exposed to harmful conditions in the event of a possible or impossible adverse event or emergency (COVID-19 infection, acute exacerbation of illness, life-threatening situation). We will take proactive steps to provide appropriate treatment and care to patients who have adverse events during the trial.

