### Statistical analysis

The SPSS (version 23.0) is used for data management and statistical analysis. The kolmogorov-Smirnov test is used for normality test. The normality data are expressed as mean ± SD, and the skewness data are expressed as median and quartile spacing. An intention-to-treat analysis will be used to assign participants whether or not they complete the intervention. Lost result data will be processed using a mixed-mode approach. Each protocol is then examined, including only patients who completed all outcome measures and followed the intervention protocol. Comparisons of baseline differences between groups will be made using one-way analysis of variance (ANOVA) or nonparametric tests. The training-related effects are evaluated using a 2 × 2 ANOVA (group × time). Differences in each group of variables over time (time effect, from baseline to 3 months) will be assessed using either a paired T-test or a nonparametric test. To detect differences between categorical variables, the Chi-square test will be applied. Bilateral *P* values < 0.05 are considered significant. In addition, the effects of different interventions on Lung function have been found in previous studies, and disease severity may be an important factor. Therefore, in order to investigate differences in effectiveness based on disease severity, a pre-designated subgroup analysis will be conducted.

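### The safety rules do not separate stopping exercise from leaving follow-up, which risks informative loss of the 3-month outcome, mainly in the exercise arms, and undermines the intention-to-treat analysis

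*Protocol article*

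**What the plan says.** The Safety section grades its responses. Reaching the heart-rate limit, or feeling discomfort, leads to a temporary measure. An emergency leads further: after chest pain, severe breathlessness, nausea and dizziness, the list ends "or injuries such as falls during exercise, patients will be asked to discontinue the trial". In the next sentence the experimenter records the patient's condition and is to "make a clear determination regarding the trial" and whether it continues.

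The section on criteria for discontinuing or modifying allocated interventions has a second rule, covering COVID-19 infection, acute exacerbation and life-threatening situations: "The trial will be stopped if a participant is exposed to harmful conditions". It names no arm.

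The Control group section describes usual care "without intervention for exercise".

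On analysis, the Statistical analysis section says: "An intention-to-treat analysis will be used to assign participants whether or not they complete the intervention". It adds: "Lost result data will be processed using a mixed-mode approach". A further analysis is restricted, "including only patients who completed all outcome measures and followed the intervention protocol". The Sensitivity analysis section plans robustness checks "using multiple imputations and assumptions regarding the missing data". The Outcome measurement section gives two time points, so the only value after baseline is the one at 3 months.

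**The concern.** An intention-to-treat comparison that is indifferent to completing the intervention needs outcomes from patients who stop exercising. A rule that asks such patients to discontinue the trial works against this unless the text says their outcomes are still collected, and it does not.

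The loss would not be random. Severe breathlessness or a fall plausibly goes with a poor walking distance and poor lung function, which are the primary outcomes. Nor would it be balanced, because the Safety rule is written around exercise sessions and control patients have none. Exercise-arm means would then lean on patients who tolerated the training and be set against a less selected control arm. The likely direction favours exercise.

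With one assessment after baseline, an early leaver contributes baseline data only, and that patient's 3-month value rests wholly on the missing-data model.

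**Working it through.** **1. The passages side by side**

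- The Safety section contrasts temporary measures with discontinuing the trial. Against that contrast, the latter reads more naturally as leaving the study than as ending a session.
- The discontinuation section is headed as a matter of interventions, but its text speaks of stopping the trial. It can be read as ending the intervention or as ending participation.
- The Statistical analysis section presumes that patients who do not complete the intervention can still be analysed.

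No sentence links the three by saying whether the 3-month assessment goes ahead after a stop.

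**2. The plan's own figures**

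Inputs from the Sample size section: difference 54 m, SD 57 m, two-sided 0.05, power 80%, 30% loss.

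- Normal approximation: 2 × [57 × (1.960 + 0.842) / 54]² = 17.49, so 18 per group. The t-test version gives 18.50, so 19, as the plan states.
- Loss: 19 / 0.7 = 27.14. The plan gives 27. Rounding up gives 28, and 5 × 28 = 140, the stated total.

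The 30% is expected loss from all causes in every group. It is not a forecast of exercise emergencies.

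**3. Bias of a completer comparison (illustration)**

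Let q be the share of an exercise arm lost after events, S the mean 6MWT distance of those who stay, and D the amount by which leavers would have fallen below S. The documents give neither q nor D, so both are assumptions.

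- All-randomised mean = (1 − q)S + q(S − D) = S − qD.
- Completer mean minus all-randomised mean = q × D.

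Type I error uses the normal approximation with SD 57, 28 controls all observed and 28(1 − q) exercise patients: SE = 57 × √(1/[28(1 − q)] + 1/28), then 1 − Φ(1.96 − qD/SE) + Φ(−1.96 − qD/SE).

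Example, q = 20% and D = 54 m: bias 0.20 × 54 = 10.8 m; observed 22.4; SE 16.16; ratio 0.668; type I error 0.103.

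| q | D = 27 m | D = 54 m | D = 108 m |
|---|---|---|---|
| 5% | 1.4 m; 0.051 | 2.7 m; 0.054 | 5.4 m; 0.064 |
| 10% | 2.7 m; 0.053 | 5.4 m; 0.064 | 10.8 m; 0.106 |
| 20% | 5.4 m; 0.063 | 10.8 m; 0.103 | 21.6 m; 0.267 |
| 30% | 8.1 m; 0.077 | 16.2 m; 0.162 | 32.4 m; 0.488 |

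Over this grid the bias runs from 2.5% to 60% of the 54 m target.

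**4. What the table leaves out**

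- Loss in control. The bias of the difference is q_E × D_E − q_C × D_C. Equal loss and equal D in both arms give zero. With 20% against 10%, both at D = 54 m, it is 10.8 − 5.4 = 5.4 m.
- Baseline data. A model that uses baseline reduces the bias to the part of D that baseline does not explain. That part remains if the model assumes missing at random, because the event happens after baseline and no later measurement reflects it.

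**The case against.** The strongest reply is that the wording is loose, not a settled rule of removal. The Safety section uses study terms loosely for exercise sessions elsewhere, its next sentence provides for a decision on continuation, and nothing says assessments cease. The other rule stands under a heading about interventions and applies to control patients as well. All randomised patients stay in the analysis, with a method for lost data and a sensitivity analysis whose unspecified assumptions could include departures from missing at random. The choice of such scenarios is ordinary SAP content. The illustrative figures describe completer means, not the planned model.

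Much of this stands. A reader might infer that event patients' outcomes are certainly removed, that this happens only in the exercise arms, and that the intention-to-treat label is therefore false. The documents do not support that. Removal is one reading and is subject to a later decision, the second rule names no arm, and methods for missing data are planned. Nor do the documents support a bias of any particular size.

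What remains is more than a detail left to the SAP. A stated rule, followed as worded, sends patients out of the trial and conflicts with a stated analysis. An undefined case-by-case decision does not resolve the conflict, and may itself make missingness selective if the person deciding knows the arm.

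**Conclusion.** The point holds as a conflict between stated sections with a foreseeable statistical consequence. The Safety and discontinuation rules do not distinguish ending the intervention from ending follow-up. Taken as written, they risk informative loss of the only outcome after baseline, mainly in the four exercise arms, and so undermine the intention-to-treat analysis without defeating it. Analyses under missing at random may not repair this. Multiple imputation on that assumption would share the main analysis's weakness, and the article does not commit to anything beyond it.

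The size cannot be fixed from the documents. With an assumed D of 54 m, a completer comparison is off by 2.7 m at q = 5% and 16.2 m at q = 30%. The second is an upper bound for that D, because it treats all planned loss as event-driven and ignores loss in control. The conclusion rests on three assumptions: that patients with events would have done worse at 3 months than those who stay, that events occur more often with trial exercise than without, and that the mixed-mode approach means a mixed model under missing at random.

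**What to change.** Reconcile the Safety, discontinuation and Statistical analysis sections, leaving the clinical decision on when exercise stops untouched:

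- State that stopping the intervention does not by itself end study participation.
- State that the scheduled 3-month outcomes (6MWT, lung function, HRCT, mMRC and SGRQ) are still sought when the patient is able, unless consent to data collection is withdrawn.
- Add at least one missing-not-at-random scenario to the sensitivity analysis: reference-based imputation, with exercise-arm leavers imputed from control, or a delta adjustment over a stated range.
- Report missing 3-month outcomes and their reasons by arm.

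The cost is a change of wording, a few extra attendances at an assessment already in the schedule, and some analysis time. Exercise estimates may become less favourable. The Trial status section says recruitment was complete at submission, so some 3-month visits may already have passed. The sensitivity analysis and the reporting by arm remain feasible even then.
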